### 2.4 Infant Morbidity During Follow-Up

For the Preterm Follow-up Study, we will use an indicator of morbidity at entry and an extended version for the follow-up itself. The protocol states (see section 2.1) that the study will exclude newborns  $\leq 26^{+0}$  weeks (only ~3% of all preterm newborns) because of the very high morbidity/mortality in this group and need for very special intensive care. A detailed protocol describing clinical conditions, "minimum criteria", for inclusion in the final growth curves will be prepared a priori before any data analysis is undertaken. Babies that do not meet the "minimum criteria" will nevertheless be followed up to form a subgroup for comparative analysis with the "healthy" preterm infants. Efforts will therefore be made to standardize the major components of infant care throughout the participating institutions. The protocol will focus on definitions that can be made operational across institutions. Criteria are likely to include any morbidity severe enough to have a negative impact on growth, feeding or the feasibility of measuring the infants at the required times.

### 2.5 Infant Feeding Practices

We expect newborn feeding to be protocol driven and based on a) the recent WHO recommendations (Edmond and Bahl "Optimal feeding of low-birth-weight infants" WHO, 2006) and b) standard NICU practice for clinical status. Descriptive data, collected in an adapted version of the WHO MGRS form, will serve to document that the centres conformed to recommended feeding patterns and clinical practice. The comparison with intrauterine charts is an important, biological secondary objective, but the main objective of the PPFS is to describe the postpartum growth that can be expected, or aspired, to by "healthy preterm newborns".

It is anticipated that all the sites will adhere to internationally recommended standards for feeding preterm infants; see review (36). The recommended first choice for LBW infants is breastfeeding or mother's own expressed milk. This is associated with the lowest incidence of infection and necrotizing enterocolitis, and best outcomes in terms of neurodevelopment. Where that is not possible, the next best choice is donor human milk and, in third place, preterm infant formula (Edmond and Bahl "Optimal feeding of low-birth-weight infants" WHO, 2006).

### 3 NCSS: to develop Newborn Birth Weight for Gestational Age Standards (Activity 3)

#### 3.1 NCSS Individual Entry Criteria

The Newborn Cross-Sectional Study will include a) all babies born to mothers in FGLS and b) all other babies born at the study centres during a fixed 12 month period. The vast majority of babies will have had their gestational age confirmed by an early ultrasound because all the hospitals included in INTERGROWTH-21st sites should already have a policy of checking gestational age with an early dating scan. Measures will be taken during the study period to reinforce this policy to ensure that all newborns have their gestational age at birth corroborated by ultrasound scan estimation early in pregnancy. The strategy of including the complete newborn population will allow us to study a large number of LBW infants and subgroups under a wide range of conditions that can affect these outcomes. We will also be able to compare the total populations across centres in terms of socio-demographics and pregnancy outcomes to confirm that the populations contributing to the new standards have the required characteristics.

##### 3.1.2 Constructing the Standards

For construction of the birth weight for gestational age standards, babies born to mothers without health problems likely to influence fetal growth will be selected from the total number of births at each centre. However, the total population of newborns during the same study period will be used to explore Objective III (determinants of LBW and its components, preterm delivery and impaired fetal growth, under current healthcare conditions). In addition, we plan to use an outcome-based approach, based on recent recommendations.a

#### 3.2 NCSS Anthropometric Measurements

All babies born during the study period will have these anthropometric measures taken within 24 hours of delivery: weight, length and head circumference. To select those newborns eligible for the NCSS (newborn standards), we will use the same criteria as for the fetal growth study.

Standardized, electronic, digital, newborn weighing scales with a precision of 10 grams will be used and their calibration status will be checked daily; they will be replaced if they are faulty and cannot be repaired. We shall also provide all clinics with standardized infantometers for length (precision 0.1 cm) and tape measures for head circumference (precision 0.1 cm); these will be similarly calibrated and maintained. All anthropometrists will be trained centrally and monitored during the study following standard procedures by the Anthropometric Standardization Unit; they in turn will train the nurses/midwives in how to apply the study's measurement protocol. We will follow the same procedures used in MGRS to certify before and during the study all staff responsible for taking the measurements, as was the case in our own previous randomized trials. As in MGRS, routine data collection will comprise duplicate measurements of weight, length and head circumference taken independently by two anthropometrists. They will check maximum allowable differences between their replicate measurement values immediately the measurements. These maximum allowable differences are approximately twice the Technical Error of Measurement of a well-trained observer (e.g. 0.7 cm for length and 0.5 cm for head circumference). If the maximum allowable difference is exceeded, the anthropometrists will immediately go on taking other duplicate measurements until the difference is acceptable. Replicate measurement values will be averaged before analysis to increase accuracy further.

#### 3.3 NCSS Quality Control Measures

The same quality control measures and standardization strategy (adapted from the WHO Child Growth Study protocol) (7) which are described above for PPFS will be employed for the three measurements to be taken for the whole study population in NCSS. A special Anthropometric Data Quality Control Unit, independent of the Study Coordinating Unit, will

a Joseph KS, Fahey J, Platt R et al. (2009) An outcome based approach for the creation of fetal growth standards: do singletons and twins need separate standards? *Am J Epidemiol* 169:5:616-624

be responsible for the monitoring and quality control of these measurements during the entire study.

### 3.4 Follow-up of the NCSS

All newborns during the study period, including those on NICU or special care, will be followed on a daily basis until hospital discharge to detect neonatal death and document severe morbidity. We will make strenuous efforts to coordinate and promote evidence-based care for the preterm neonates using materials developed as part of the WHO best practice programme, by liaising with the lead neonatologist in each NICU before and during the study. We recognize that differences in practice will persist despite our best efforts. However, we believe this is unavoidable in a very pragmatic study such as this, which is trying to reflect what happens on a daily basis in clinical practice. Furthermore, we will similarly make strenuous efforts to standardize the main protocols for feeding practices in each NICU before the study starts. During the routine site-visits by members of the Study Coordinating Unit and the Anthropometric Team we will monitor the implementation of the protocols.

### 3.5 Biological Samples

We have debated the issue of anonymized genetic/epigenetic data at great length. In principle, we would not wish to miss an opportunity to put together what would be a unique databank. However, we are very concerned about a) the effect that a request to collect DNA might have on recruitment rates; b) ethical questions that might be raised by IRBs; c) the additional time required to obtain informed consent, and d) the extra cost of processing the samples. Having said this, it nonetheless remains an important issue. Therefore, we shall bring together a group of international experts and potential academic partners, to discuss the advantages and disadvantages of collecting biological samples for a specific hypothesis relating to fetal growth and/or preterm delivery. The final decision will depend largely on whether the study has sufficient power to answer a specific question, relating for example to the effect of a genetic polymorphism on a pregnancy outcome. After much discussion, it was finally decided to collect biological samples from FGLS and NCSS pregnancies from 2011 onwards. For details of biological sample collection refer to Section 1.11 and Appendix K.

### 3.6 Severe Perinatal Morbidity and Mortality Outcomes

Birth weight for gestational age standards will be related to indicators of perinatal outcome to establish risk levels associated with different growth patterns. The 'ideal' outcome is perinatal mortality, but its anticipated infrequent occurrence in this low risk population makes it unrealistic to have a sample large enough for the necessary number of events across the gestational age distribution (perinatal mortality is expected to be close to 1% in these populations). We have therefore decided to use an un-weighted composite outcome including at least one of the following conditions: stillbirth, neonatal death until hospital discharge of the newborn, newborn stay in NICU for  $\geq 7$  days or other severe neonatal complications. We have used such an outcome recently (12, 13); it requires limited standardization of clinical diagnoses across hospitals and is well accepted as a marker in large, international, population based studies of newborns that are severely ill.b It could be argued, however, that intrapartum stillbirth may not be related to fetal growth and should not be included in this index. We believe this is a valid point but as it will not be possible to separate those intrapartum deaths that are related to IUGR from those that are unrelated, we suggest keeping the index as it is. As we expect a very low fetal death rate, it should not have a major impact on the observed rates.

We believe this is a good proxy for adverse perinatal outcomes across countries. We have used it as a primary neonatal outcome in recent publications and it has been well accepted. Its only disadvantage is that it risks excluding from the total number of early neonatal deaths some cases amongst healthy, mostly term babies delivered vaginally who, after hospital discharge at 48 hours, develop severe complications or death up to 7 days

b Others have also used these composite indices of neonatal morbidity (Hannah ME, Hannah WJ Kewson SA et al (2000); Wapner RJ, Sorokin Y, Thom EA (2006); Joseph KS, Fahey J, Platt R (2009))

post-natally without returning to the same hospital. However, missing these isolated cases is preferable to performing thousands of unnecessary home visits.

Data from our population-based studies in some of the sites indicate that the incidence of this outcome is close to 5%. We will confirm this estimate during the preparatory phase of the study in the study centres. We will also reach consensus with the investigators and consultants on the few very severe clinical conditions to be included in the composite outcome in addition to perinatal death and  $\geq 7$  days NICU stay.

#### 4. On-line Data Management and Statistical Analysis

All data will be entered into an on-line data management system specifically developed for the study; it will include a system for direct transfer of blinded data from the ultrasound machines to the database. This on-line system has the practical benefit of allowing on-going quality control, correction of errors or missing values and the initiation of data analysis soon after data collection is completed. We have previously used such a system in very large multi-centre studies (12) and randomized clinical trials in developing countries, and we are confident that there will be few problems in adapting this concept to the proposed study. The system will be field tested during 2008 using the data flow model shown in Appendix B.

This system will be used for data management and monitoring all sub-studies, including patient recruitment and follow-up, and is based on the INTERGROWTH-21st Electronic Data Management System (IDAMIS). The system permits all participants' data to be incorporated contemporaneously into the data files via the Internet. Included within the system is a review process to ensure that all data are complete, and that the research team is notified about imminent patient visits and expected delivery dates. At an institutional level, each centre will have its own progress enrolment charts and weekly recruitment targets. The system will also provide the Data Coordinating Unit with a detailed daily record of patient enrolment and data entry, at both individual and institutional levels to monitor progress against the milestones listed in the protocol. Corresponding actions, such as telephone calls, web conferences or site visits will take place within a week of detecting a problem in a centre to ensure that appropriate corrective measures are introduced. Lastly, the system will allow the database to be analyzed as soon the data collection period has ended.

Data from all sites will be pooled to construct the curves for international applications using the WHO Child Growth Study analytical strategy (8). Data analysis will be conducted following the same strategy used in the construction of the WHO MGRS curves during Years 3-5. It will be coordinated by the Statistical Director ([name]), consultant statistician/epidemiologist and the team's senior investigators. Extensive secondary analyses of these data will be conducted including the development of velocity standards, thereby contributing in a major way to answering questions relating to clinical practice and public health now and for years to come.

The appropriateness of pooling data from all sites will be assessed by comparisons of site means, standard deviations and the 3rd and 97th centiles to the pooled values of primary data. Consistent differences  $\geq 0.5$  SD between the mean values of individual sites and the pooled sample will be used as a pre-set trigger for considering whether to adjust by site for purposes of pooling data. This has to be supported by site-specific consistent differences across primary measures. For the WHO-MGRS it was concluded that data from all sites were remarkably similar and thus should be pooled (8). This is the strongest biological argument to date and will be the basis for the conceptualization of our analysis.

The planned approach will be based on the experience of the WHO-MGRS adapted to the fetal growth parameters (37); we shall follow the same exploratory strategy used in this study. We are aware that these analyses may not be automatically applicable, but we feel comfortable that the considerable experience of this team of statisticians in carrying out a similar study will enable them to select a final model that is fit for purpose. The methods do not require similar intervals. We are not making any assumptions about the shapes of the individual curves, except that they will be smooth.

For the physical growth standards, a class growth distribution that can fit the data for all measurements will be explored with an appropriate smoothing technique to generate centiles. Candidate distributions (e.g. Box-Cox  $t$ , modulus-exponential-normal, Box-Cox-power-exponential, Johnson's  $S_U$  or Johnson's  $S_B$ ) will be compared on the basis of goodness of fit for each age group using the following diagnostic tools: (a) Log-likelihood

comparisons, (b) Q-Q plots (i.e. comparing empirical and distributional centiles), and (c) Comparisons of observed percentages that occur below estimated centiles against expected values. Once the most appropriate distribution(s) for our data is (are) identified, smoothing techniques will be tested against the same diagnostic criteria applied to the selection of distributions such as polynomial smoothing, the Box-Cox  $t$  distribution that smoothes using natural splines and a variation of it with the Box-Cox-power-exponential distribution. [name] (University of Oxford Statistics Department) who advised us on another pregnancy-based study, will be invited to contribute to the selection process.

It could be argued that only parous women should be included in the construction of the standards. Furthermore, it would reduce the incidence of LBW babies amongst the mothers recruited as nulliparous women are known to be at higher risk of LBW babies. However, it is also the case that long-term outcomes in newborns born to parous versus nulliparous women have similar overall morbidity and mortality rates. Overall, we believe that the advantages of recruiting solely parous women are outweighed by the loss in external validity and credibility in doing so. Therefore, we intend including all women regardless of parity but we will try to recruit similar proportions across the study sites. We will also explore in the analysis if, in this sample of healthy women, parity is an important effect modifier for fetal growth, but we do not expect to produce parity-specific fetal growth standards. In addition, based on the same biological principles, sex-specific charts should be constructed for fetuses as they have been for newborns. However, we do not plan to separate fetuses by sex as this is not a routine practice and it is unlikely that it will become one in the future. Conversely, separate sex-specific charts will be developed to monitor the postnatal growth of preterm babies.

## 5. Sample Sizes for Objective I (Activities 1 - 3)

**General principles:** The precision of growth chart centiles is determined by several factors, of which the most important is sample size. Other factors are also relevant, including study design (cross-sectional vs. longitudinal), the timing of measurements, and the method of curve-fitting. Many criteria can be used to estimate sample size, but three are considered critical here, namely the precision of: a) a given centile at a particular gestational age; b) the logistics of selecting and following-up a large cohort, and c) the rate of the expected perinatal outcome for Activity 3, in Objective I. (The outcomes to be used in Objectives II-III are either continuous variables or far more prevalent than severe neonatal morbidity/mortality, i.e. a preterm delivery rate of 9-10%, and therefore sample size limitations are of less concern for these parts of the study). Sample sizes have been estimated taking each of these criteria into account. The numbers quoted below are combined figures for all study sites.

It is possible that the WHO-MGRS findings of similar infant growth patterns amongst different ethnic groups may not apply to fetal growth, even though recent data for US white/black newborns support the concept of pathological rather than physiological factors being responsible for observed variations (16). We question why fetuses should grow differently to infants or be affected differently by environmental influences, or why biologically different growth patterns should exist across ethnic groups. Nevertheless, we will make all practical efforts to obtain the largest possible sample size per ethnic group to allow separate evaluation in case the alternative hypothesis (different fetal growth by ethnic group) is observed. Even if this is the case for some groups it is very unlikely that all ethnic groups will have biologically relevant different growth patterns.

**FGLS:** To obtain complete data from 4,000 pregnancies at 8 study sites, 500 mothers will have to be enrolled at each centre. Data from previous years will be used at each study site to estimate the expected number of eligible women available and the recruitment rates. We expect that ~75% of the total pregnant population at the sites selected will be eligible for this cohort, although local investigators will be strongly advised to be conservative in their estimates of compliance rates and to allow for attrition due to other reasons. The 4,000 women should provide close to 800 cases of each of the 5 general ethnic groups. Sample size calculations (15), based on a width of the 95% CI of the 5th birth weight percentile of 2.5% at term (2,700g), demonstrate that 600 women per ethnic group should be adequate, after excluding complicated pregnancies and women lost to follow-up. This sample size is larger than most previous studies and adequate, we believe, to produce reliable curves.

However, we will not produce ethnic-specific standards because such pregnant populations are rarely representative of a unique ethnic group, particularly in urban areas in developing and developed countries. It would therefore be impractical to alternate between standards based on each patient's ethnic classification, even if this could be done. We will not be able to estimate outcomes across groups with any degree of power but that is not an objective of this study. These numbers should also fulfill the requirements for PPFS of ~360 preterm infants (assuming a preterm rate of 9% based on our previous study involving similar populations (12)).

We estimated that fewer than 5% of women will be lost to follow up (the figure is usually ~ 3% in our large trials). We also adjusted for the fact that 10-15% of women will be excluded from the preparation of the fetal growth standards because they will have developed problems severe enough to have affected fetal growth.

**PPFS:** A cohort of ~360 preterm babies will be recruited from FGLS for this study. It is expected that the gestational age distribution will provide 310 babies >30 weeks gestation. Only the subgroup of babies free of major clinical problems will be used to create the standards. We recognize that the sample size calculation here is influenced by logistic issues and the availability of newborns from FGLS rather than statistical calculations. However, it is still large by preterm study standards and we shall have very detailed follow-up data. We consider that the possibility of having a full set of fetal and newborn growth patterns from a cohort of preterm newborns is a biological priority even if we shall not have the power to explore other subgroup analyses such as gestational age sub-groups or early postnatal morbidity. Postnatal growth from healthy populations has been shown to be similar among ethnic groups (38, 39).

**NCSS:** The sample size calculations for this component of the study depend mostly on the number of preterm newborns needed at the lower end of the gestational age distribution and the perinatal outcome selected. A fixed data collection period (12 months) is planned for all hospitals but it is clear that some variability will have to be accepted considering the size of each institution and the population characteristics. From the pool of all newborns, we will select the ones born to eligible women using the FGLS criteria listed above. We expect the refusal rate to be minimal. We will aim for a total of 50,000 newborns with very detailed information which will provide, based on data from similar institution (40), a sample of ~75% eligible babies for the newborn charts, including ~1,800 with a severe outcome using our established criteria. Of these 1,800, we expect that 70% (about 1,200) will be between 26 and 36 completed weeks of gestation.

**Missing values:** We consider that women without newborn data cannot contribute to any of the three studies. Fetal deaths and newborns with congenital malformation will be excluded. All women should have at least 2 follow-up values after the dating scan to be included in the fetal growth study.

## B. Objective II: Activities 4 - 6

Objective II will be achieved by the following three activities:

- 1) Preparation of computer files of 2D ultrasound measures for 3-week gestational windows between 20-34 weeks;
- 2) Development of analytical strategies for the construction of predictive models to estimate gestational age during mid-late pregnancy and
- 3) Completion of prediction model to estimate gestational age during mid-late pregnancy based on several ultrasound measures obtained at a single visit. Ultrasound-based gestational age estimation in infrequent attendees or women with limited access to care is usually based on a single ultrasound measure (e.g. BPD), but the estimates have large errors and wide confidence intervals. We are planning to develop equations that use several ultrasound measures obtained at a single visit. If we achieve this, it will be a major contribution to the care of high-risk women attending hospitals on only one or two antenatal visits late in pregnancy.

Statistical strategies for the production of the prediction models include multiple regression analysis using gestational age at delivery as the gold standard (dependent variable), then recalculating the expected gestational age at different time points. The independent variables or predictors will be the basic ultrasound measures at a given

gestational age window, as well as other clinical parameters that are available to the staff during the antenatal care.

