#### Secondary objectives:

- II. To develop a prediction model, based on multiple 2D ultrasound measurements, for estimating gestational age during mid-late pregnancy for use in populations of pregnant women without access to early/frequent antenatal care.
- III. To determine in this multi-ethnic sample the determinants of LBW, as well as associated conditions, e.g. preterm delivery and impaired fetal growth and their subgroups, under current healthcare conditions.
- IV. To acquire additional 3D images to create an anatomical and growth databank of individual fetal organs as a unique source of biological information for future research.

To the best of our knowledge, this project is unique because of its comprehensiveness and scale (never attempted before). It has all the characteristics recommended in the literature for constructing ideal standards for international use (6, 7): it is prescriptive, longitudinal, population-based, and gestational age will be established by ultrasound early in pregnancy. We will be able to explore associated research questions, such as possible ethnic differences in fetal/newborn growth, risk factors for LBW and its subgroups. We will also be able to predict gestational age in women with poor antenatal care and simultaneously provide a set of practical tools, which can be introduced into maternal and newborn care worldwide in a short space of time.

There is considerable demand from maternal and neonatal services to WHO and professional organizations for the standards that this study will produce (5). Hence, we have designed this project in consultation with experts in the field, as well as other research groups and institutions, in such a way that it could easily complement other yet to be developed studies, thereby reducing the risk for duplication.

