**Estimation of gestational age at study entry:** Clearly, establishing a very precise determination of gestational age is vitally important for constructing these growth standards (in addition to clinical management) and we are prepared to screen large numbers of women, if necessary, to obtain the ideal population.

There are three possibilities for gestational age estimation early in pregnancy: dating by a) LMP alone; b) early ultrasound alone or c) LMP and ultrasound. The implications of these different methods on research findings have recently been discussed (22). Dating by LMP and ultrasound is clearly an assessment of different parameters. Although it has been suggested that before 14+0 weeks of gestation ultrasound may be better by an average of 2-3 days in predicting the date of delivery, in clinical practice, both are often used in combination. Based on the 2004 Birth Cohort from the Brazilian Centre, we anticipate that 7% of women will not have a reliable LMP. In other studies in this socio-economic group, the figure may be as high as 20%.

Taking all these factors into consideration, we have decided not to base gestational age solely on LMP; rather we shall use a standard gynecological definition of LMP as the first level in calculating the gestational age. Among women with a certain LMP and regular periods who are 9+0 to 14+0 weeks pregnant, we will corroborate the gestational age with an ultrasound CRL measurement, using an internationally recognized and validated chart (23). If the difference in gestational age estimation by CRL and LMP is  $\leq 7$  days we will consider the LMP to be reliable and take it as the true biological date. It is acknowledged that we may exclude a number of women who might otherwise have been eligible if only ultrasound were used, but the aim is to define a population with as exact a gestational age at entry as possible.

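### Objective II names gestational age at delivery as the outcome of a model meant to give gestational age at the scan; and if scan age is the outcome, fitting within 3-week windows would make the reported precision look falsely good

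*Protocol*

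**What the plan says.** Protocol section VII.B (Objective II: Activities 4 - 6) lists three steps. The first is "Preparation of computer files of 2D ultrasound measures for 3-week gestational windows between 20-34 weeks". The second is to develop the analytical strategies. The third is "Completion of prediction model to estimate gestational age during mid-late pregnancy based on several ultrasound measures obtained at a single visit". The Secondary objectives in section VI.B give the intended use: "for use in populations of pregnant women without access to early/frequent antenatal care".

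The one statistical method named is "multiple regression analysis using gestational age at delivery as the gold standard (dependent variable), then recalculating the expected gestational age at different time points". The predictors are the scan measures from one "gestational age window, as well as other clinical parameters that are available to the staff during the antenatal care".

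The stated reason for the work is that dating late attenders usually rests on a single measure, "but the estimates have large errors and wide confidence intervals".

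Gestational age at every FGLS scan is already known. Section 1.1 (Estimation of gestational age at study entry) admits only women whose CRL agrees with the LMP within 7 days, in which case "we will consider the LMP to be reliable and take it as the true biological date".

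**The concern.** The quantity wanted is age on the day of the scan. The dependent variable named is age on the day of delivery. These differ by the scan-to-delivery interval, which nobody knows when a late attender is scanned. The step that is meant to bridge the two is not defined.

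The second worry concerns the windows. A model developed on scans selected by true gestational age, and judged within that selection, cannot show a large error, because the selection has already removed most of the spread in the quantity being predicted. The objective is justified by the large errors of existing methods, so a windowed analysis could appear to solve that problem through truncation alone. Users would then trust the equation more than it deserves.

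**Working it through.** The protocol gives no sample size, accuracy target or error figure for Objective II, so there is no figure to reproduce. The two issues have different sources and are checked separately.

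**1. Delivery age as the outcome**

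Write S for age at scan, D for age at delivery and I = D − S for the interval.

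- Regressing D on biometry within a window gives predictions close to the mean of D if biometry carries little information about D. In simulation (200,000 scans, 20 to under 35 weeks, four correlated measures, SD of D assumed to be 1.2 to 2.0 weeks), R² was 0.000 when fetal size was assumed unrelated to D, and at most 0.021 when a correlation of −0.2 was assumed. These values reflect the assumed correlation. They illustrate the expectation and do not prove it.
- If each woman's actual I is subtracted, the error is the residual SD of D, here 1.2 to 2.0 weeks. That is not an understatement, but I is unavailable in use.
- If the window's mean interval is subtracted, the result is mean(D) − mean(D − S) = mean(S). Every woman is given roughly the window midpoint.
- If S is recovered before the regression, D − I equals the LMP/CRL age at the scan. That is the right outcome, but the text does not state it.

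**2. Scan age as the outcome, fitted within 3-week windows**

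Inputs from the protocol are the window width of 3 weeks and the range 20–34 weeks. I read the range as completed weeks, giving five windows: 20–23, 23–26, 26–29, 29–32 and 32–35. Assumptions not in the documents are scans spread evenly within a window and a biometry scatter e, in gestational-age equivalents, rising linearly from 0.6 weeks at 20 weeks to 1.2 weeks at 35 weeks.

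- Variance of S in a window: V = 3²/12 = 0.75, so the SD is 3/√12 = 0.87 weeks (6.1 days). This caps the apparent error even when biometry is pure noise.
- Within-window slope: λ = V/(V + e²).
- Apparent error SD: √(V(1 − λ)).
- Understatement relative to e: 1 − √λ.

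| Window midpoint (weeks) | e | λ | Apparent SD | Understatement |
|---|---|---|---|---|
| 21.5 | 0.66 | 0.63 | 0.53 | 20% |
| 24.5 | 0.78 | 0.55 | 0.58 | 26% |
| 27.5 | 0.90 | 0.48 | 0.62 | 31% |
| 30.5 | 1.02 | 0.42 | 0.66 | 35% |
| 33.5 | 1.14 | 0.37 | 0.69 | 40% |

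Simulation agrees: slopes 0.63 down to 0.36, and apparent SD 0.52–0.69 weeks against 0.67–1.11 weeks for an unrestricted equation. That gives 1 − 0.52/0.67 = 22% to 1 − 0.69/1.11 = 38%.

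Varying the scatter in the four-measure simulation:

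| Scatter, 20 to 35 weeks | Apparent SD, windowed | Error by 3-week band, single equation | Understatement |
|---|---|---|---|
| 0.5 to 1.0 | 0.47–0.64 | 0.57–0.94 | 18–32% |
| 0.7 to 1.5 | 0.58–0.74 | 0.83–1.38 | 30–46% |
| 1.0 to 2.0 | 0.68–0.79 | 1.18–1.81 | 42–56% |

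**3. Error in actual use**

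A late attender must be assigned a window from her biometry. With the 0.6 to 1.2 week scatter, this gave an overall error of 0.95 weeks, against 0.86 to 0.93 weeks for a single equation depending on how that equation was fitted: 0.95/0.93 = 1.02 and 0.95/0.86 = 1.10.

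In the four-measure simulation, the root mean square over the five windows for the lowest scatter is √((0.58² + 0.71² + 0.82² + 0.94² + 0.90²)/5) = 0.80 weeks against 0.75, or 7% more. The same sum for the other two scenarios gives 1.15 against 1.09 and 1.51 against 1.44, each about 5% more. Individual bands run from about 7% less (1.29 against 1.38) to about 15% more (1.18 against 1.03).

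**The case against.** The strongest defence is that the recalculation step means back-dating. In FGLS the interval from scan to delivery is known for every woman, so delivery age minus that interval is exactly the LMP/CRL age at the scan. On that reading the outcome is right. This is plausible and would remove the first issue. But the text labels delivery age as the dependent variable and places the recalculation after the regression, so a programmer following it would fit the wrong model.

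Second, the two issues cannot both hold under one reading. Selecting scans at 20–34 weeks does not truncate delivery age: in simulation its SD stayed at the assumed 1.4 weeks in every window. Truncation arises only with scan age as the outcome. This stands, and the second issue is therefore conditional.

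Third, window-by-window fitting is partly inferred. The first activity is a file-preparation step and the third speaks of one model. This also stands in part: tying the predictors to a given window suggests separate fits but does not state them.

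Fourth, the named regression is only said to be included among the strategies, developing strategies is itself an activity, and Appendix F foresees a statistical analysis plan. Clustering, edge handling and validation can properly wait for that plan. A dependent variable that is already named, and is literally the wrong one, is more than missing detail.

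A reader might go further and infer that windowing would misdate late attenders by 1.1 to 1.7 weeks. That figure applies only to a woman actually in the next window who is given the wrong window's equation, and it takes no account of how often that happens. The near-zero R² should likewise not be cited as evidence, because it follows from what the simulation assumed.

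**Conclusion.** The point holds in two parts. First, as written, Objective II names the wrong dependent variable for its purpose and leaves undefined the step that might correct it. This needs no numerical assumption beyond the expectation that mid-pregnancy size says little about delivery date. Second, and only if scan age is the outcome and equations are fitted within the true-age windows, the apparent error SD is capped at 0.87 weeks (given even spread of scans) and is roughly 20–40% too small at an assumed scatter of 0.6 to 1.2 weeks. Across the wider range of scatter examined the understatement was 18–56%, in the same direction throughout.

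The loss of accuracy in use is small, about 0–10% overall. The damage from windowing is therefore falsely good reported precision; materially worse dating has not been shown. Recruitment, scanning and the primary growth standards are untouched. With one secondary objective affected and an inexpensive remedy, I rate this as moderate.

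**What to change.** In section VII.B, replace the dependent variable with gestational age at the scan, taken from the LMP corroborated by CRL. If back-dating from delivery was intended, say so and state that it precedes the regression.

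Fit one continuous equation over the whole range, with a margin on either side of 20–34 weeks and allowance for repeated scans of the same fetus. The margin needs no extra visits, because the schedule in section 1.4 already has scans from 14 to 42 weeks. If the 3-week files are kept for data handling, state that they do not define separate models.

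Report prediction error without selecting on the true-age window, for example by predicted age, preferably with validation on sites left out of the fit. The validation and clustering details can sit in the statistical analysis plan.

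The cost is protocol wording and analysis code, with no new data. The downside is that the reported error will look larger than a windowed analysis would show.
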